## **8. Study Assessments and Procedures**

A schedule for the tests and evaluations to be conducted in this study is found in the schedule of activities.

For all measurements, the actual date and time of assessment, including date of sampling, will be recorded in the CRF. Where a time window is acceptable, this is clearly indicated in the following sections.

### **8.1. Enrolment, Screening and randomization**

#### **8.1.1. Enrolment**

Patients' enrolment: patients will be enrolled, after written informed consent obtainment, if they meet inclusion criteria and no exclusion criteria are verified.

#### **8.1.2. Screening**

A screening form in the CRF will be completed for all patients who signed the Patient Informed Consent Document, regardless of subsequent randomization into the study. Patients will be identified by their age and sex; patient number if randomized or reasons for exclusion from the study will be recorded.

#### **8.1.3. Randomisation**

Compliance with inclusion/exclusion criteria will be finally verified through demographic, laboratory test results and clinical information.

Patients fulfilling all the inclusion criteria and none of the exclusion criteria will be randomized (randomization number assigned) by an Investigator (or designee).

Patients who do not meet the Inclusion Criteria or meet Exclusion Criteria will be considered screen failures (screen failure number assigned) and will not be allowed to be re-considered for inclusion into the study.

#### **8.1.4. Visits**

##### **T0 Visit (Day 0): Screening**

The Investigator will explain to the patient(s) the objectives of the study, benefits and risks for the patient and will answer all questions regarding the study.

Following the signature of the informed consent, the participant's inclusion/exclusion criteria will be assessed.

This visit includes:

- Signature of informed consent
- Evaluation of Inclusion and exclusion criteria
- Demography
- Past and current medical conditions
- Pregnancy test (WOCBP only)
- Blood withdrawal for hepatic and muscle functionality

##### **Randomization and data collection**

This includes:

Randomization

- IMP supply (1 kit) and instructions for IMP handling
- Full physical examination
- Medical history (includes substance usage)
- 12-lead ECG
- ECHO

- CMR
- Holter ECG
- ICD/ILR interrogation
- Psychological questionnaires (i.e. Short Form Health Survey 36 (SF-36) [26] ; Hospital Anxiety and Depression Scale (HADS) [27]; Impact of Event Scale-Revised (IES-R)) [28] (see Annex IVa, Annex IVb and Annex IVc)
- Blood withdrawal for genetics, if needed
- Blood withdrawal for biomarkers

#### **T2 Visit Safety check (2nd month +/- 1 month)**

This visit includes:

- IMP supply (**2kits**)
- Full physical examination
- Pregnancy test (WOCBP only)
- Blood withdrawal for hepatic and muscle functionality
- Patient-reported outcome collection
- Study treatment adherence check
- AE review
- SAE review

#### **T4 Visit Safety check (4nd month +/- 1 month)**

This visit includes:

- Full physical examination
- Pregnancy test (WOCBP only)
- Blood withdrawal for hepatic and muscle functionality
- Patient-reported outcome collection
- Study treatment adherence check
- AE review
- SAE review

#### **T9 Visit Data collection (9th month +/- 1 month)**

This visit includes:

- IMP supply (3 kits)
- Full physical examination
- Pregnancy test (WOCBP only)
- Blood withdrawal for hepatic and muscle functionality
- 12-lead ECG
- ECHO
- Holter ECG
- ICD/ILR interrogation
- Psychological questionnaires (i.e. SF-36; HADS; IES-R)
- Blood withdrawal for biomarkers
- Patient-reported outcome collection
- Study treatment adherence check
- AE review
- SAE review

#### **T12 Phone call, safety check (12th months +/- 1 month)**

This visit includes:

- Patient-reported outcome collection
- Study treatment adherence check
- AE review
- SAE review

#### **T15 Phone call, safety check (15th months +/- 1 month)**

This visit includes:

- Patient-reported outcome collection
- Study treatment adherence check
- AE review
- SAE review

#### **T18 Visit, data collection (18th month +/- 1 month)**

This visit includes:

- Full physical examination
- Blood withdrawal for hepatic and muscle functionality
- Pregnancy test (WOCBP only)
- 12-lead ECG
- ECHO
- CMR
- Holter ECG
- ICD/ILR interrogation
- Psychological questionnaires (i.e. SF-36; HADS; IES-R)
- Blood withdrawal for biomarkers
- Patient-reported outcome collection
- Study treatment adherence check
- AE review
- SAE review

#### **Follow-up Phone call, end of the study (19th month +/- 1 month)**

This visit includes:

- Patient-reported outcome collection
- AE review
- SAE review

## **8.2. Discontinuation/Withdrawal Criteria**

### **8.2.1. Discontinuation of Study Treatment**

Definitive treatment discontinuation for individual subjects may occur due to undesirable effects related to the systemic use of oral IMP as follows: severe allergic reaction; serious skin conditions; serious muscle weakness, soreness, pain or breakage or change in color of the urine (rhabdomyolysis) (rare;  $\geq 1/1,000$ ); unusual bleeding or bruising, suggesting a liver disorder; Lupus-like illness syndrome (very rare;  $< 1/10,000$ ).

The SMB will evaluate further “stopping rules” or “discontinuation criteria” based on side effects registered during the trial.

All definitive treatment discontinuation reasons and dates should be recorded by the investigators in the appropriate CRF page when considered as confirmed.

The study will be stopped if any of the following are found:

- i. a death possibly/probably related to the IMP;
- ii. treatment discontinuation (> 15% patients) due to severe adverse effects (SAEs) related to the systemic use of oral IMP.

If the IMP administration is prematurely discontinued the primary reason for discontinuation must be recorded in the CRF.

See the SoA for data to be collected at the time of treatment discontinuation and follow-up and for any further evaluations that need to be completed.

### **8.2.2. Temporary Discontinuation of the Study Treatment**

Temporary treatment discontinuation is allowed (i.e. failing to take medication for  $\leq 15$  consecutive days).

### **8.2.3. Withdrawal from the Study**

Patients will be informed that they have the right to withdraw from the study at any time (withdrawal of consent), without prejudice to their medical care, and are not obliged to state their reasons. Patients who have withdrawn consent to the study or who for any cause have discontinued the study cannot be reincluded in it. Investigators may decide to discontinue the study for a patient for any clinical problem, or if other issues arise (such as, for example, non-compliance with the Protocol, etc.).

The withdrawal or discontinuation of the patient from the Study must be documented in the CRF. If a patient fails to return to the centre for a scheduled visit, attempts should be made to contact the patient to ensure that the reason for not returning is not a SAE. Likewise, if a patient declares his/her wish to discontinue from the study e.g. for personal reasons, an attempt should be made to establish that the true reason is not a SAE (bearing in mind the patient is not obliged to state his/her reasons).

Safety laboratory tests should be performed whenever possible at patient withdrawal.

It is also possible for the study to be terminated prematurely by the Sponsor in case of:

- new information leading to an unfavorable risk-benefit assessment of the IMP, such as occurrence of previously unknown significant adverse reactions or unexpectedly high intensity or incidence of known adverse reactions, or other unfavorable safety findings;
- Trial no longer justified for clinical or ethical reasons;
- withdrawal of IMP from the market for safety reasons.
- Finally, the trial could be terminated or suspended at the request of health authorities.

If the study will suffer of more than the expected 15% of dropout, the endpoints will be calculated anyway, as a proof of principle. In case of missing data to achieve the aims, these will be imputed using multiple imputation and a sensitivity analysis will be performed on the imputed data.

### **8.2.4. Lost to Follow-Up**

A participant will be considered lost to follow-up if he or she repeatedly fails to return for scheduled visits and is unable to be contacted by the study site.

The following actions must be taken if a participant fail to return to the clinic for a required study visit:

- The site must attempt to contact the participant and reschedule the missed visit as soon as possible and counsel the participant on the importance of maintaining the assigned visit schedule and ascertain whether or not the participant wishes to and/or should continue in the study.
- Before a participant is deemed lost to follow-up, the investigator or designee must make every effort to regain contact with the participant (where possible, 3 telephone calls and,

if necessary, a certified letter to the participant's last known mailing address or local equivalent methods). These contact attempts should be documented in the participant's medical record.

- Should the participant continue to be unreachable, he/she will be considered to have withdrawn from the study with a primary reason of lost to follow-up.

### **8.3. Adverse Events**

Adverse event (AE) evaluations will be performed during the whole duration of the study, starting from the time of signing of the Informed Consent and up to the end of the study.

#### **8.3.1. Definitions**

##### **8.3.1.1. Adverse Event**

An Adverse Event (AE) is defined as any untoward medical occurrence in a subject to whom a medicinal product is administered and which does not necessarily have a causal relationship with this treatment.

An AE can therefore be any unfavourable and unintended sign (including an abnormal laboratory finding), symptom, or disease temporally associated with the use of a medicinal product, whether or not related to the medicinal product.

##### **8.3.1.2. Adverse Reaction**

An Adverse Reaction (AR) is defined as a response to a medicinal product which is noxious and unintended and which occurs at doses normally used in man for the prophylaxis, diagnosis or therapy of disease or for the restoration, correction or modification of physiological function.

An AR can therefore be any unfavourable or unintended change in the structure (signs), function (symptoms), or chemistry (lab data) in a participant to whom an IMP has been administered and related to any dose administered. Medication errors, pregnancies and uses outside what is foreseen in the protocol, including misuse and abuse of the product, shall be subject to the same obligation to report as adverse reactions.

##### **8.3.1.3. Serious Adverse Event**

A serious adverse event (SAE) is defined as any untoward medical occurrence that at any dose requires inpatient hospitalisation or prolongation of existing hospitalisation, results in persistent or significant disability or incapacity, results in a congenital anomaly or birth defect, is life-threatening, or results in death.

An important medical event that based upon appropriate medical judgment, may jeopardize the patient and may require medical or surgical intervention to prevent one of the outcomes listed above is also an SAE.

Symptoms or medically significant laboratory or instrumental (e.g., electrocardiographic) abnormalities of a pre-existing disease, such as cancer or other disease, should not be considered an adverse event. However, occurrence of new symptoms, or laboratory or instrumental abnormalities, as well as worsening of pre-existing ones, are considered adverse events. Planned procedures that require hospitalization will not be considered SAEs.

##### **8.3.1.4. Serious Adverse Reaction**

A serious adverse reaction (SAR) is defined as an adverse reaction which results in death, is life-threatening, requires inpatient hospitalization or prolongation of existing hospitalization, results in persistent or significant disability or incapacity, or is a congenital anomaly/birth defect, or a medically important/clinically significant event.

#### **8.3.1.5. Unexpected Adverse Drug Reaction**

An unexpected adverse drug reaction is adverse event, the nature or severity of which is not consistent with the applicable product information (e.g., Investigator's Brochure for an unapproved investigational product or summary of product characteristics for an approved product).

#### **8.3.2. Recording of adverse events**

The Investigator is responsible for detecting, documenting, and reporting events that meet the definition of an AE or SAE.

Information on AEs should be obtained through observation of the patient, from any information volunteered by the patient, or through patient questioning.

All AEs (serious and non-serious) which occur from the signature of the informed consent until the final follow up visit will be recorded in the eCRF. The Investigator must provide information on the adverse event, preferably with a diagnosis, or at list with sign and symptoms; start and stop dates (and start and stop time if the adverse event lasts less than 24 hours); intensity; causal relationship to IMP; action taken and outcome.

Adverse events must be recorded individually, except when considered manifestations of the same medical condition or disease state; in such cases they must be recorded under single diagnosis. The Investigator must also provide start and stop dates (and start and stop time if the adverse event lasts less than 24 hours); intensity; causal relationship to IMP; action taken and outcome.

All AEs and SAEs must be followed until resolution, until the condition stabilizes, until the event is otherwise explained or until the patient completes the study or is lost to follow-up. The Investigator is responsible to ensure that follow-up includes any supplemental investigations as may be indicated to elucidate as completely as practical the nature and/or the causality of AE/SAE. This may include additional laboratory tests or investigations, or consultation with other health care professionals.

##### **8.3.2.1. Seriousness of AE**

When an AE occurs in a patient who has been administered at least one dose of the IMP, the Investigator responsible for the care of the subject must first assess whether the event is serious using the definition given in paragraph 8.3.1.3.

If the event is serious, then a Safety Report form must be completed and the CVBF Safety Management Team notified according to the procedure described in section 8.3.3.3.

##### **8.3.2.2. Relationship of AE to the IMP**

The Investigator will assess the possible relationship between the AE and the IMP, according to the following criteria:

- Reasonable possibility of a relatedness with study medication
- No reasonable possibility of relatedness with study medication

The expression "reasonable possibility of relatedness" is meant to convey in general that there are facts (evidence) or arguments that suggest a causal relationship. The Investigator will be also asked to consider the following before reaching a decision on causality assessment:

- time relationship between study drug intake and event's onset;
- medical history;
- lack of efficacy/worsening of existing condition;
- study treatment(s);
- mechanism of action of the investigational product;
- class effects;
- other treatments-concomitant or previous;
- withdrawal of study treatment(s);
- de-challenge (did the event abate after stopping drug?);

- re-challenge (did the event reappear after reintroduction?);
- erroneous treatment with study (or concomitant) medication;
- protocol related process.

### 8.3.2.3. Severity of AEs

Grading the intensity (severity) of a specific event is not the same as declaring it as "serious", which is based on patient/event outcome or action criteria usually associated with events that pose a threat to a patient's life or functioning. Seriousness (not severity) serves as a guide for defining regulatory reporting obligations.

The Investigator will grade the severity of all AEs using the definitions in the **Table below**. For each episode, the highest severity grade attained should be reported.

|          |                                                                                                                                      |
|----------|--------------------------------------------------------------------------------------------------------------------------------------|
| Mild     | Grade 1 - Does not interfere with patient's usual function (awareness of symptoms or signs, but easily tolerated [acceptable]).      |
| Moderate | Grade 2 - Interferes to some extent with patient's usual function (enough discomfort to interfere with usual activity [disturbing]). |
| Severe   | Grade 3 - Interferes significantly with patient's usual function (incapacity to work or to do usual activities [unacceptable])       |

### 8.3.3. Serious Adverse Events Reporting

If an AE meets at least one seriousness criterion, this becomes an SAE and must be reported to the CVBF Safety Management Team as follows:

- The Investigator records the event in the patient's medical records and in the Adverse Event Form of the eCRF, indicating the seriousness of the event and the result of the causal relationship with the IMP assessment.
- The Investigator reports the SAE, regardless of presumed causal relationship, to CVBF Safety Management Team (delegated by the Sponsor) by e-mail (preferred) or fax within 24 hours of learning of the event. Contact details for SAE reporting are provided in the section "Study Personnel" of the protocol under Pharmacovigilance.

Expedited reporting (i.e., the notification within 24 hours of awareness of the event) must be carried out:

- from signature of informed consent up to the final follow-up visit (serious adverse event).
- with no time limitation if the event is likely to be related to the IMP (serious adverse reaction).

#### 8.3.3.1. Notification process

Information on SAEs will be recorded in the Safety Report Form (SRF). Copy of the SRF will be archived in the Investigator's Site File. Follow-up reports (as many as required) should be completed and faxed/e-mailed following the notification procedure described below.

Whenever more than one SAE is observed, the Investigator should identify which is the primary adverse event, i.e. the most relevant one. If other events are listed in the same report, the Investigator, along with their relatedness to the IMP, should identify which adverse events are serious and which are non-serious. In any case, the Investigator is requested to record his/her opinion about the relatedness of the observed event(s) with the investigational medication.

#### **Initial**

The SRF must be completed by the Investigator or by his/her authorised delegate with all available information at the time of notification and then emailed or faxed to the CVBF Safety Management

Team within 24 hours of awareness of the event together with any extra annotated information/copies of test results.

Even if the Investigator has minimal information to include in the initial report (i.e., identifiable reporter, identifiable patient, a suspected investigational product, an adverse event), it is important that he/she always makes an assessment of causality to the IMP and/or concomitant medication and/or research event for every event prior to transmission of the SRF. The Investigator may change his/her opinion on causality in light of follow-up information and notify this change by sending a follow up SRF.

### ***Follow-up***

Patients must be followed-up until resolution of all queries, clinical recovery is complete and laboratory results have returned to normal baseline, or until progression has been stabilised, or until the patient is lost to follow-up. Follow-up may therefore continue until after the subject has left the study, if necessary.

Follow-up information should be recorded in a new SRF and sent by email/fax to the CVBF Safety Management Team as information becomes available. All relevant additional information (hospital discharge letter, blood analyses, etc.) should be attached to the SRF.

The subject must be identified by patient's ID and date of birth only. The patient's name should not be used on any correspondence and should be erased from any additional information provided.

### **8.3.3.2 Regulatory Reporting Requirements for SAEs**

The CVBF Safety Management Team will review all SRFs received.

The causality assessment given by the Investigator will not be overruled and in case of disagreement, both opinions will be provided in any reports.

The CVBF Safety Management Team will comply with regulatory requirements relating to safety reporting to regulatory authorities and will also assure that all Investigators are informed of any safety issues that arise during the course of the trial.

All suspected unexpected serious adverse reactions (SUSARs), which occur with the investigational products within this clinical trial, will be submitted in compliance with the timelines and standards for reporting SUSARs set out in the Regulation (EU) no 536/2014 and linked guidance.

The concerned Regulatory Authorities will be informed via EudraVigilance and the Investigators by periodic line-listings.

### **8.3.4. Cardiovascular and Death Events**

Not applicable.

### **8.3.5. Disease-Related Events and/or Disease-Related Outcomes Not Qualifying as AEs or SAEs**

The following disease related events (DREs) are described in patients with Arrhythmogenic cardiomyopathy and can be serious/life threatening:

- Death for cardiac arrest.
- ICD intervention for VT.
- Cardiac-related syncope.
- Hospitalization for heart failure.

These events are rare, but typically associated with the disease under study. They will not be reported according to the standard process for expedited reporting of SAEs even though the event

may meet the definition of a SAE. These events will be recorded on the patient's eCRF within 3 days.

However, if either of the following conditions applies, then the event must be recorded and reported as an SAE (instead of a DRE):

- The event is, in the investigator's opinion, of greater intensity, frequency, or duration than expected for the individual patient.

OR

- The investigator considers that there is a reasonable possibility that the event was related to treatment with the investigational product.

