#### **9.1.2 Analysis of efficacy variables**

SEARCH TRIAL first aim is to provide evidence of Atorvastatin clinical efficacy in preventing ACM deterioration. The variable used to determine efficacy in the primary endpoint is the progressive decline of RV free wall longitudinal strain measured by ECHO at T18.

The variables used to determine efficacy in the secondary endpoint at T18 are i) arrhythmia burden (PVC, non-sustained and sustained VA, VF, appropriate ICD shocks); ii) other morphological parameters (ventricular volumes, function, both at ECHO and CMR); iii) ECG parameters; iv) blood parameters.

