#### **9.1.3 Analysis of safety variables**

AEs will be presented in terms of the number of AE, the incidence, severity and relationship to the study drug, overall and by body system and preferred term. SAEs will be presented in the same way.

Results for routine laboratory tests will be assessed as being below the lower limit of the normal range, within the normal range or above the upper limit of the normal range. The frequency of patients reporting an abnormal or abnormal clinically significant laboratory value at screening and follow-up will be presented for each laboratory variable. Vital signs will be presented using descriptive statistics.

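### Cardiac-arrest death, cardiac syncope and heart failure admission are recorded and listed, but set apart from the AE/SAE tables and assigned to no comparison between arms

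*Protocol*

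**What the plan says.** Section 8.3.5 is headed "Disease-Related Events and/or Disease-Related Outcomes Not Qualifying as AEs or SAEs". It names four events: death from cardiac arrest, ICD intervention for ventricular tachycardia, cardiac syncope and hospitalisation for heart failure. The body is narrower than the heading. It lifts the expedited process ("They will not be reported according to the standard process for expedited reporting of SAEs even though the event" may meet the SAE definition) and keeps the data: "These events will be recorded on the patient's eCRF within 3 days".

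Two conditions return an event to SAE status. The first is: "The event is, in the investigator's opinion, of greater intensity, frequency, or duration than expected for the individual patient". The second is: "The investigator considers that there is a reasonable possibility that the event was related to treatment with the investigational product". An event that meets either one is handled as an SAE in place of a disease-related event, so the two classes are mutually exclusive.

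For analysis, section 9.1.3 states: "AEs will be presented in terms of the number of AE, the incidence, severity and relationship to the study drug". It treats SAEs in the same way and adds laboratory results and vital signs. Section 9.1.2 names "arrhythmia burden (PVC, non-sustained and sustained VA, VF, appropriate ICD shocks" together with other morphological, ECG and blood parameters. Section 8.3.4, on cardiovascular and death events, is marked as not applicable.

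In section 8.2.1 the SMB considers further stopping or discontinuation criteria on the basis of registered side effects. One ground there for stopping the study is "a death possibly/probably related to the IMP". Section 8.3.2.2 grades causality on two levels only: a reasonable possibility of relatedness, or none.

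**The concern.** The synopsis hopes that atorvastatin will delay progression toward heart failure and reduce electrical instability. Cardiac-arrest death, heart failure admission and syncope are the clinical form of those outcomes, and they are also where harm resembling the disease would appear. Once they are classed as disease-related events they leave the AE/SAE tables, and no other table by arm takes them in.

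The two routes back to SAE status do not fill the gap. Each is one investigator's opinion about one patient, and section 7.4 keeps investigators blinded. An event that is unremarkable for each patient can still be more frequent in one arm, and only a count by arm shows that.

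**Working it through.** **1. Where each event goes under the protocol as written**

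| Event in 8.3.5 | AE/SAE tables (9.1.3) | Efficacy variables (9.1.2) | Recorded and listed (8.3.5, 9.3) |
|---|---|---|---|
| Death from cardiac arrest | only if escalated | no (VF episodes overlap in part) | yes |
| ICD intervention for VT | only if escalated | largely, through sustained VA and appropriate shocks | yes |
| Cardiac syncope | only if escalated | no | yes |
| Heart failure hospitalisation | only if escalated | no | yes |

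Three of the four have no named comparison between arms. Section 9.3 lists all CRF data by patient and centre, but a listing is not a summary by arm.

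**2. Passages that do not agree**

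- 8.3.1.3 makes death and inpatient hospitalisation seriousness criteria and counts worsening of pre-existing symptoms or abnormalities as adverse events. The heading of 8.3.5 says that the listed events do not qualify as AEs or SAEs, while its body concedes that they may meet the SAE definition.
- 8.3.3 has every SAE reported within 24 hours whatever the presumed causality. 8.3.5 exempts these events unless the investigator escalates them.
- 8.2.1 uses a possible/probable causality wording. The scale in 8.3.2.2 has two levels and contains neither term.

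**3. Size of the trial, from its own figures**

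Inputs from section 9.1: difference 2.4, SD 4.5, one-sided alpha 0.05, power 80%.

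n per group = 2 × (1.645 + 0.842)² × (4.5 / 2.4)² ≈ 43.5, rounded up to 44. This matches the protocol. Adding 15% gives 44 × 1.15 = 50.6, rounded up to 51 per arm, or 102 in all. This also matches.

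**4. What a table by arm could show**

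The protocol gives no event rate. The rates below are assumptions for illustration, with 51 patients per arm.

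- Expected patients with an event: 51 × 0.02 = 1.0 and 51 × 0.05 = 2.6, so about 1–3 per arm.
- If an arm has no events, the one-sided 95% upper limit for its rate is 1 − 0.05^(1/51) = 5.7%.
- Chance that a true excess gives a two-sided Fisher p<0.05 (exact binomial enumeration):

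| Assumed true rates | Expected patients | Chance of p<0.05 |
|---|---|---|
| 2% vs 10% | 1.0 vs 5.1 | 20% |
| 2% vs 15% | 1.0 vs 7.7 | 52% |
| 5% vs 10% | 2.6 vs 5.1 | 7% |
| 5% vs 15% | 2.6 vs 7.7 | 25% |
| 5% vs 20% | 2.6 vs 10.2 | 52% |

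Even a tripling would usually miss significance. Counts by arm would still show the imbalance, which single-case escalation cannot do.

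**The case against.** The strongest reply is that little is lost. The body of 8.3.5 removes expedited reporting, not recording. The events reach the eCRF within 3 days and the listings in 9.3, unusual or possibly related cases must be reported as SAEs, and section 10.1 has deaths and life-threatening problems reported to the ethics committee without exempting disease-related events. A separate SAP or an SMB charter may exist, and table layouts commonly belong there. With so few events expected, a table would rarely be conclusive.

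Much of this stands, and it rules out several stronger readings that a reader might infer:

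- *The events would go unreported.* They are recorded and listed, some become SAEs, and deaths go to the ethics committee.
- *The SMB would not see them.* Section 8.2.1 states one task of the board, not everything that it receives. The supportable statement is that the protocol names no route.
- *Patients who die before T18 would appear only as missing strain values.* Section 9.1.4 plans to examine whether drop-out is linked to disease events and allows for a post-hoc correction, and 8.2.3 requires discontinuation to be documented.
- *All four events escape comparison.* ICD intervention for VT is largely inside the arrhythmia-burden endpoint.
- *Marking 8.3.4 as not applicable means that deaths will not be analysed.* It does not say so; it simply leaves the section empty.

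The appeal to a separate SAP answers less than it seems to. Section 9.3 says that the analysis plan is described in the protocol itself, and the mutually exclusive classes in 8.3.5 are a stated rule, not an omitted detail. Followed as written, that rule keeps these events out of the tables that 9.1.3 promises. The contradictions among 8.3.1.3, 8.3.3 and 8.3.5 also lie within this document.

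**Conclusion.** The point holds in this form: the protocol moves cardiac-arrest death, cardiac syncope and heart failure hospitalisation out of AE/SAE status unless a blinded investigator escalates the single case. It then assigns them to no comparison between arms and to no named SMB review. This rests on the wording of 8.3.5, 9.1.2 and 9.1.3 and does not depend on any event rate.

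The size in patients cannot be derived from the documents. The 1–3 per arm above assumes rates of 2–5%, and the protocol says only that the events are rare. The consequence is an incomplete safety comparison, not hidden data. It is worth correcting because these are the most serious outcomes in the trial and the data needed are already collected.

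**What to change.** - In 9.1.3, add a descriptive table by arm, in the Safety population, of each disease-related event and of all-cause death (patients with an event and number of events). Place it beside the SAE tables and attach no significance test.
- State that cumulative counts of disease-related events by arm are provided to the SMB.
- In 8.3.4, replace the not-applicable entry with a pointer to this table.
- Reconcile the heading and body of 8.3.5 with each other and with 8.3.1.3 and 8.3.3.
- Reconcile the causality wording in 8.2.1 with the two-level scale in 8.3.2.2.

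The expedited reporting rules need not change for this. The cost is one extra table, one listing for the board and a few sentences of protocol text, with no new data collection.
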